### Interim analyses {21b}

No interim analysis will be performed.

### Methods for additional analyses (e.g., subgroup analyses) {20b}

There is no plan to conduct any subgroup or adjusted analyses.

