### Outcomes {12}

#### Outcomes

##### Main outcome

Difference between the two groups on endothelial function measured by FMD (change of percentage of dilatation of brachial artery diameter from baseline) and PAT (change of reactive hyperemia index of finger from baseline) after 8 week of intervention.

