### Sample size {14}

Based on the effect size estimate of 0.3 standard deviations in the response of endothelial function after HCQ, for a 95% power and 0.05 level of alpha error probability, the sample size was estimated at 20 participants per group. Allowing for extra recruitment to compensate for losses, the sample size will be 25 participants per group, with a sum of 50 individuals.

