## Statistical methods

### Statistical methods for primary and secondary outcomes {20a}

Normally distributed data will be presented as mean and standard deviation. Data not normally distributed will be presented as median and interquartile range. The natural logarithmic transformation of the variable will be used to correct its non-normal distribution in analyses that assume the normal data distribution. The intervention arm (hydroxychloroquine) will be compared against the control for all primary analysis. We will use chi-squared test for binary outcomes, and *T* test for continuous outcomes. We will examine the residual to assess model assumptions and goodness-of-fit. The group × time interaction will be tested using generalized estimating equations. We will use the Bonferroni method to appropriately adjust the overall level of significance for multiple primary outcomes, and secondary outcomes. Results with a probability < 0.05 of alpha error will be considered statistically significant. Statistical analyses will be performed using SPSS software (SPSS Inc., Chicago, IL, USA).

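### For continuous outcomes the plan names two tests without saying which decides, and plans no baseline adjustment, which usually costs precision against ANCOVA

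*Protocol article*

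**What the plan says.** The two main outcomes, in Outcomes {12}, are both change scores: for FMD, "change of percentage of dilatation of brachial artery diameter from baseline", and for peripheral arterial tonometry, "change of reactive hyperemia index of finger from baseline". The continuous secondary outcomes are defined in the same way.

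Statistical methods {20a} assigns the tests: "We will use chi-squared test for binary outcomes, and *T* test for continuous outcomes". The same paragraph adds: "The group × time interaction will be tested using generalized estimating equations". It does not say which result decides, and it gives no variance estimator or reference distribution for the GEE. It applies a Bonferroni adjustment across primary and secondary outcomes, but not across two tests of one outcome.

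Methods for additional analyses {20b} then states: "There is no plan to conduct any subgroup or adjusted analyses". Read together, these sections plan an unadjusted comparison of changes and leave no place for a baseline-adjusted one.

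On size, Sample size {14} says that "the sample size was estimated at 20 participants per group", raised to 25 per group to allow for losses.

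**The concern.** Each continuous outcome is measured once at baseline and once at 8 weeks. A change score gives the baseline a fixed coefficient of 1. ANCOVA estimates that coefficient, and when the two measurements are only moderately correlated the estimated coefficient is well below 1 and the treatment contrast is more precise. The change score then over-corrects a chance baseline imbalance. With 20 to 25 per group such imbalances can be noticeable. The protocol itself says, in its background on flow-mediated dilatation, that small differences in method can affect FMD results and reduce reproducibility, so a correlation well short of 1 is plausible.

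The second issue is the missing hierarchy. With two p-values for one question and no rule, the choice between them can be made after both are known. What is at stake is precision that could be had from data already collected, and a clear answer to which test a claim of significance rests on.

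**Working it through.** **Inputs.** From the protocol: 1:1 allocation, 20 evaluable per group (25 with the allowance for losses), outcomes as change from baseline, alpha 0.05, two primary outcomes. Assumed: equal variances at the two visits, complete data, and a correlation ρ between baseline and 8 weeks of 0.3 to 0.7, because the protocol gives none.

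**The plan's own figure.** The stated inputs are "Based on the effect size estimate of 0.3 standard deviations in the response of endothelial function after HCQ" and "for a 95% power and 0.05 level of alpha error probability". The two-sided two-sample formula gives n = 2 × (1.960 + 1.645)² / 0.3² ≈ 289 per group (241 one-sided), not 20. At 20 per group, power for 0.3 SD is about 15%. This is a separate and larger problem. It matters here only because ANCOVA cannot be expected to solve it.

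**Precision.** With outcome variance σ² at each visit and n per group:

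- T test on change: variance of the group difference = (2σ²/n) × 2(1 − ρ).
- ANCOVA: (2σ²/n) × (1 − ρ²) × [1 + 1/(2n − 4)]. The bracket is the cost of estimating the slope; at n = 20 it is 37/36.
- Ratio, ANCOVA to change: [(1 + ρ)/2] × 37/36.

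| Assumed ρ | (1 + ρ)/2 | × 37/36 | Equivalent extra participants (1/ratio − 1) |
|---|---|---|---|
| 0.3 | 0.65 | 0.67 | 50% |
| 0.5 | 0.75 | 0.77 | 30% |
| 0.7 | 0.85 | 0.87 | 14% |
| 0.9 | 0.95 | 0.98 | about 2% |

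The ratio reaches 1 at ρ = 2 × 36/37 − 1 ≈ 0.95. Above that, the change score is marginally better at this size.

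Simulated power at 20 per group, two-sided 5%, change score then ANCOVA, for ρ = 0.3, 0.5 and 0.7:

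- True difference 0.9 SD: 65% to 82%, 79% to 88%, 95% to 97%.
- True difference 0.3 SD: 12% to 16%, 15% to 18%, 22% to 25%.

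**The two tests.** With two visits and complete data, the GEE interaction estimate is exactly the difference in mean change, so it shares its point estimate with the T test on change. Only the standard error and reference distribution can differ.

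If the GEE used an uncorrected robust variance with a normal reference, its variance would be too small by the factor (n − 1)/n, and its size would be P(|t with 2n − 2 df| > z × √((n − 1)/n)):

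- n = 20, nominal 5%: P(|t₃₈| > 1.960 × √(19/20)) = 6.4%. At nominal 2.5% (Bonferroni over two primary outcomes): 3.5%.
- n = 25: 6.1% and 3.3%.
- T test and ANCOVA: 5.0%.

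Under that assumption, declaring success when either test is significant also has an error of 6.4% at 20 per group.

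**The case against.** The strongest reply is that nothing here is an error. A T test on change in a randomised trial is unbiased, holds its size and does use the baseline; preferring ANCOVA is a matter of efficiency. The {20b} sentence stands under additional analyses and does not by its own words govern the primary analysis. The trial calls itself exploratory, and ANCOVA would leave it badly underpowered for 0.3 SD.

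Much of this stands. The absence of adjustment in the primary analysis is inferred from {12}, {20a} and {20b} together. The inference is sound, since {20a} names only unadjusted tests and {20b} says no adjusted analyses are planned. The criticism is of efficiency and clarity, not validity.

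A reader might infer four stronger things that the protocol does not support:

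- *That the planned GEE exceeds its nominal error rate.* The protocol does not state the variance estimator or any correction, details that an article may leave to a fuller document. The 6.4% is conditional, and modest even then.
- *That every outcome has two competing tests.* Binary outcomes are assigned only a chi-squared test. For continuous ones, with complete data, both tests use the same estimate. An either-test error near 10% arises only if the T test is run on week-8 values, and the outcome definitions point to change.
- *That ANCOVA always wins, by 54%, 33% or 18% in participants.* Those figures come from (1 + ρ)/2 without the cost of the slope, which matters at 20 per group.
- *That switching is free of drawbacks.* The Discussion and Trial status sections report that data were analysed, a result was seen and recruitment will not resume.

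**Conclusion.** The point holds as one of efficiency and clarity. For continuous outcomes the protocol names two tests with no rule for which decides, and plans no adjustment for the baseline value. Relative to ANCOVA, the T test on change gives up the equivalent of about 14% to 50% more participants if ρ lies between 0.7 and 0.3, assuming equal variances and 20 per group. It gives up almost nothing at 0.9 and nothing at about 0.95. The range for ρ is an assumption and the gain depends strongly on it.

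The T test itself is valid. Any inflation from the GEE, 6.4% at 20 per group or 6.1% at 25, depends on an uncorrected robust Wald test that the protocol does not specify. The change is worth making, but it does not rescue the sample size: with ANCOVA, power for 0.3 SD stays at about 16% to 25%.

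**What to change.** In Statistical methods {20a}, name one primary analysis for each continuous outcome: ANCOVA of the 8-week value on randomised group and the baseline value of that outcome, reported with a t-based 95% confidence interval. Reword {20b} to say that no adjusted analyses are planned other than for the baseline value of the outcome. Drop the GEE test, or keep it as a declared sensitivity analysis with a small-sample-corrected variance.

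The cost is a few sentences. Baseline values are already collected and SPSS fits the model directly. There is one small downside: data have already been examined, so the change must be labelled as made after data were seen, and the T test on change that the protocol planned should be reported alongside. The sample-size statement in {14} needs its own correction.

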### Methods in analysis to handle protocol non-adherence and any statistical methods to handle missing data {20c}

Participants who withdraw consent for continued follow-up will be included in the analysis by modern imputation methods for missing data. The effect that any missing data might have on results will be assessed via sensitivity analysis of augmented data sets.

## Oversight and monitoring

### Composition of the data monitoring committee, its role and reporting structure {21a}

Due to the short duration of the trial and known minimal risks, a data monitoring committee is not needed.

### Adverse event reporting and harms {22}

Hydroxychloroquine use may have potential risks for the participants. It is possible that the ingestion of the drug causes side effects (loss of appetite, emotional instability, headache, blurred vision, pain in the belly, nausea, itching, and spots on the skin), described in the informed consent. To monitor these side effects, follow-up phone calls will be made every four weeks and adverse events will be investigated for open-ended questions, including general symptoms, such as headache, nausea, and blurred vision. An adverse event that meets the criteria for a serious adverse will be reported to the institutional ethics committee. A serious adverse event for this study is any untoward medical occurrence that is believed by the investigators to be causally related to study-drug and results in any of the following: life-threatening condition, severe/permanent disability, or prolonged hospitalization

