## Assignment of interventions: Blinding

### Who will be blinded {17a}

Trial participants, researchers involved in the study, outcome assessors will be blinded.

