### Frequency and plans for auditing trial conduct {23}

There is no plan for auditing trial conduct.

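### The serious adverse event definition makes investigator-believed causality a condition of seriousness and omits death and new, non-prolonged admission, so serious events judged unrelated would not reach the ethics committee

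*Protocol article*

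**What the plan says.** The section Adverse event reporting and harms {22} gives a definition specific to this trial. A serious adverse event is "any untoward medical occurrence that is believed by the investigators to be causally related to study-drug" and that "results in any of the following: life-threatening condition, severe/permanent disability, or prolonged hospitalization". Both parts must be met.

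The same section states the reporting rule: "An adverse event that meets the criteria for a serious adverse will be reported to the institutional ethics committee". It gives no other route to the ethics committee.

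Ordinary adverse events are collected separately: "follow-up phone calls will be made every four weeks and adverse events will be investigated for open-ended questions". Strategies to improve adherence {11c} also describes calls that ask about adverse effects. (The call interval differs between these two sections; that is a separate matter to reconcile.) The only harms outcome, under Secondary outcomes, compares the rate of adverse effects between the groups.

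On oversight, section {21a} holds that "a data monitoring committee is not needed", and section {23} states: "There is no plan for auditing trial conduct". On blinding, section {17a} states: "Trial participants, researchers involved in the study, outcome assessors will be blinded".

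**The concern.** Seriousness describes what happened to the participant. Causality is an opinion about why it happened. The definition merges the two, so the opinion decides whether the event is classed as serious at all. In a placebo-controlled trial the control arm supplies the background rate of serious events, and that comparison needs every such event, whatever anyone thought caused it.

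The population makes this more than a drafting matter. Participants are over 65 with an apnea-hypopnea index above 15, and the abstract calls elderly people with sleep apnea vulnerable to heart disease. A cardiac event in such a person has a ready explanation other than the capsule. An investigator who does not know the arm could reasonably call it unrelated, and the event would then fall outside the definition.

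What is at stake is external notice of serious events, and a complete account of them in the final report.

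**Working it through.** No figure in the protocol depends on this definition, so there is nothing to recompute. The check is to apply the wording to each kind of serious outcome, and then to look for any other section that would widen it.

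**Step 1. Inputs.** From section {22}: the causality condition, the three listed results, and the reporting trigger. From {17a}, {21a} and {23}: blinding, the absence of a monitoring committee and the absence of audit.

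**Step 2. Apply the definition.** An event qualifies only if it is believed related AND has a listed result.

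| Outcome of the event | Believed related | Believed unrelated |
|---|---|---|
| Death | Only if read into the life-threatening criterion | No |
| Life-threatening, survived | Yes | No |
| Severe or permanent disability | Yes | No |
| Prolonged hospital stay | Yes | No |
| New admission, not prolonged and not otherwise listed | No | No |

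Of the 5 × 2 = 10 combinations, 3 clearly qualify, 1 depends on a generous reading, and 10 − 3 − 1 = 6 do not qualify. Of those 6, 5 fail on causality alone or on causality and the list together (the whole right-hand column). The remaining 1 fails only because the list is short. These are categories, not expected numbers of events.

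**Step 3. Follow the consequence.** The reporting sentence covers only events that meet the criteria, so the 6 combinations that do not qualify carry no duty to inform the ethics committee.

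**Step 4. Look for a second route.** Sections {11b}, {11c}, {17b}, {21a}, {22}, {23} and Secondary outcomes were compared. None widens the definition or sends deaths, admissions or unrelated events anywhere else. Reporting to the ethics committee is the only external safety route described, and it runs through this definition.

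**Step 5. Separate classification from recording.** The calls seek adverse events with no stated causality condition. An event judged unrelated can therefore still be written down as an ordinary adverse event. What it loses is the label of serious and the report to the ethics committee.

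**The case against.** The strongest case on the other side has five parts.

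- **Events are not lost.** A reader might infer that serious events judged unrelated go uncounted altogether. The documents do not support this. Collection through the calls carries no causality filter, and the definition has one stated use, which is reporting to the ethics committee. This part stands and limits the point to classification and reporting.
- **No planned comparison is damaged.** A reader might also infer that a between-arm analysis of serious events would be emptied. The protocol plans none. The secondary outcome concerns the rate of adverse effects and does not refer to the serious event definition. This stands. Any table of serious events by arm is an addition proposed here.
- **The list can be read generously.** A death believed to be drug-related would naturally be read as life-threatening, and a long new admission could pass as prolonged hospitalisation. It would be wrong to say that all deaths fall outside the criteria. This stands, but such a reading does nothing for events judged unrelated, and a definition should not need it to capture death.
- **Attribution is blinded.** The documents show no differential bias between arms, because investigators are not meant to know the allocation. This largely stands. However, section {17b} allows unblinding for severe adverse effects, and the article does not say that causality is judged beforehand. Blinding also does not restore the missing report.
- **The trial has stopped.** The Discussion says that the project was abandoned as designed, and Trial status says that recruitment will not resume. An amendment would protect no future participant. This stands, and it moves the remedy to the events already recorded.

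It cannot be said that a fuller document may cure this. The article states the definition as the one for this study; it is not a detail left out for brevity.

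**Conclusion.** The point holds as a defect in a stated rule. Causality is a condition of seriousness, and the closed list omits death and new, non-prolonged admission. With no monitoring committee and no audit, a death, life-threatening event or admission judged unrelated would be neither classed as serious nor reported to the ethics committee.

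Its size cannot be given as a number of events. The documents state no serious event rate and no count of events to date. They plan 25 participants per group, 50 in all, and do not say how many were enrolled; 4 subjects were lost when the centre closed. The practical effect may be nil if no such event occurred.

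The conclusion assumes that the definition is followed as written. The remaining benefit is mainly retrospective, and it assumes that the adverse event records hold enough detail to be reclassified.

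**What to change.** **Definition.** In section {22}, delete the causality condition and complete the list. For example: *a serious adverse event is any untoward medical occurrence, whether or not considered related to study drug, that results in death, is life-threatening, requires a new hospital admission or prolongs an existing one, or results in severe or permanent disability.* Record the investigator's view of causality as a separate field, made blind to arm and before any unblinding.

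**Retrospective application.** Re-screen the adverse events already recorded for every randomised participant, including any who withdrew or were excluded because new care was started under {11d}. Report newly qualifying events to the ethics committee.

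**Final report.** Tabulate all serious events by randomised arm regardless of attribution, with causality shown alongside. Present this as descriptive, since no such comparison was planned. If the records are too thin to classify an event, say so.

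**Cost.** One amended sentence, one extra field, a re-check of the records of at most the 50 planned participants, and possibly a few more ethics reports. No analysis of efficacy changes.

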### Frequency and plans for auditing trial conduct {23}

There is no plan for auditing trial conduct.

### Plans for communicating important protocol amendments to relevant parties (e.g., trial participants, ethical committees) {25}

Important protocol changes as well as changes in eligibility criteria, outcomes, or analyses will be communicated to the investigators, institutional ethics committee, trial participants, and trial registries.

### Dissemination plans {31a}

The investigators will communicate relevant trial results to participants by telephone call and printed material. The publication in a peer-reviewed journal is mandatory for the thesis author to have her PhD title acknowledged. The results database will be made available at the university repository.

## Discussion

The COVID pandemics forced changes in protocol. The research center was closed and volunteers were instructed to cancel the visits. This incurred in the loss of 4 subjects. An interim analysis was performed to check for the need to continue recruiting. A new sample size calculation was performed. The large number necessary to obtain 80% power made the project unviable. The investigators decided to abandon the project as initially designed. The finding of a small but significant reduction in the OSA severity may be hypothesis-generating. We may continue searching for possible inflammatory mechanisms and therapeutic targets of OSA.

## Trial status

The recruitment began on 03/19. Due to the changes in protocol during the COVID pandemic, recruitment will not be resumed.

## Data Availability

Not applicable.

## Abbreviations

HCQ: Hydroxychloroquine
OSA: Obstructive sleep apnea
NO: Nitric oxide
FMD: Flow-mediated dilation
PAT: Peripheral artery tonometry
RHI: Reactive hyperemia index
TNF-α: Tumor necrosis factor alpha
